### Statistical analysis

True positive and true negative diagnoses will be defined according to the hospital discharge record retrieved by site investigators at each participating hospital. Contingency table analysis will allow reporting of sensitivity, specificity, positive predictive and negative predictive rates for the logistic score, with CIs determined by sample size. The development and validation data sets will be further explored for model refinement using a logistic regression approach, with the same entry variables entered into forward selection, removal from models at p<0.1, and significance ascribed at p<0.05. An ROC curve will be reported for rAAA diagnosis using the original logistic score, and the refined score at the study end. Separate logistic models will be designed to explore 30-day mortality. Where diagnosis or mortality data cannot be retrieved, ROC analysis is impossible. As per STROBE guidelines, this study will fully describe the available data for patients with diagnoses/mortality and those without diagnosis/mortality, and subject the demographics/presenting features of both cohorts to statistical comparison to explore whether the absence of diagnosis data has introduced selection bias to the study.

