**Methods and analysis:**

Prospective multicentre observational study assessing the diagnostic accuracy of a prehospital smartphone triage tool for detection of rAAA. The study will be conducted across London in conjunction with London Ambulance Service (LAS). A logistic score predicting the risk of rAAA by assessing ten key parameters was developed and retrospectively validated through logistic regression analysis of ambulance records and Hospital Episode Statistics data for 2200 patients from 2005 to 2010. The triage tool is integrated into a secure mobile app for major smartphone platforms. Key parameters collected from the app will be retrospectively matched with final hospital discharge diagnosis for each patient encounter. The primary outcome is to assess the sensitivity, specificity and positive predictive value of the rAAA triage tool logistic score in prospective use as a mob app for prehospital ambulance clinicians. Data collection started in November 2014 and the study will recruit a minimum of 1150 non-consecutive patients over a time period of 2 years.

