**Trial registration number:**

CPMS 16459; pre-results.

Strengths and limitations of this studyProspective multicentre observational study across major city.Large number of patient cases in target population.Use of mobile technology to facilitate accurate data collection.Assessment and validation of clinical decision-making tool for prehospital diagnosis of ruptured abdominal aortic aneurysm.Potential for non-random patient selection and confounding introducing bias.Reliant on accurate documentation of final hospital discharge diagnosis for each patient encounter.Incomplete data entry sets are not saved.

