### Inclusion criteria

All patients over the age of 18 years assessed by a LAS clinician with acute abdominal/back/chest pain or collapse requiring transfer to hospital who do not fulfil entry criteria for existing triage tools such as myocardial infarction (MI), stroke and major trauma during the recruitment period will be eligible for inclusion.

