
### Primary outcome

To assess and validate the sensitivity and specificity of the rAAA smartphone triage tool

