### Power calculation

Modelling from HES data covering the period 2005–2010 estimates that over a 12-month period 150 rAAA and over 1000 controls (ie, patients found not to have a rAAA) will be studied. The study will recruit a minimum of 1150 non-consecutive patients. Expected CIs associated with predicted model performance are as follows: 83% sensitivity (95% CI 75.9% to 88.2%); 73% specificity (95% CI 69.0% to 78.3%). The expected ROC curve characteristic will have an area under the curve statistic of 0.85±0.01.

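### PPV is primary in the abstract but not in the Primary outcome section, and a PPV read from the recruited sample's 2x2 table cannot be assumed to transfer to triage use

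*Protocol article*

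**What the plan says.** The protocol article states the primary outcome twice. In the abstract (Methods and analysis): "The primary outcome is to assess the sensitivity, specificity and positive predictive value of the rAAA triage tool logistic score". Under Primary outcome: "To assess and validate the sensitivity and specificity of the rAAA smartphone triage tool". The Statistical analysis section covers predictive values without ranking them: "Contingency table analysis will allow reporting of sensitivity, specificity, positive predictive and negative predictive rates for the logistic score".

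On the sample, the Power calculation section says "The study will recruit a minimum of 1150 non-consecutive patients" and expects that "over a 12-month period 150 rAAA and over 1000 controls (ie, patients found not to have a rAAA) will be studied". It plans on "83% sensitivity (95% CI 75.9% to 88.2%); 73% specificity (95% CI 69.0% to 78.3"%). Eligibility is set by symptoms: adults "assessed by a LAS clinician with acute abdominal/back/chest pain or collapse requiring transfer to hospital", outside the existing triage pathways. The strengths and limitations list concedes "Potential for non-random patient selection and confounding introducing bias".

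The Smartphone triage tool section adds that eligible patients not entered in the app cannot be followed up. It regards this as no limitation, because the study's aim is sensitivity and specificity. The Secondary outcomes section plans a model of cost and workload, including the consequences for false-positive patients, if the tool decided the destination of a patient in whom rAAA is suspected.

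**The concern.** There are two linked problems.

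First, the two statements of the primary outcome differ on PPV. This is a contradiction within the article and cannot be put down to condensing a longer document.

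Second, PPV depends directly on prevalence. A PPV taken from the study's own 2x2 table describes the recruited case mix. That mix depends on which patients clinicians enter on their own phones, and the sampling is openly non-consecutive. The article's reassurance about patients who are not entered appeals only to sensitivity and specificity, so it gives no cover to a PPV that the abstract calls primary.

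False positives are central to the study's purpose. The Background, Secondary outcomes and Discussion all ask what diversion would mean for patients without rAAA and for vascular centres. If the recruited sample held a higher share of rAAA than the population triaged in practice, the raw PPV would make diversion look more acceptable than it is.

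**Working it through.** **Inputs** (all from Power calculation): 150 rAAA; over 1000 controls; minimum 1150 patients; sensitivity (Se) 83%; specificity (Sp) 73%. Only the point values are used; the stated confidence intervals play no part.

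**Step 1: the plan's own figure.** 150 + 1000 = 1150, which reproduces the stated minimum. Planned prevalence is 150/1150 = 13.04%. With 150 cases this is an upper value, since controls are put at over 1000.

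**Step 2: the 2x2 table the plan implies.**

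- True positives: 0.83 × 150 = 124.5
- False negatives: 150 − 124.5 = 25.5
- False positives: 0.27 × 1000 = 270
- True negatives: 0.73 × 1000 = 730
- PPV = 124.5/(124.5 + 270) = 31.6% (95% CI about 27% to 36%)
- NPV = 730/(730 + 25.5) = 96.6%
- False positives per true positive = 270/124.5 = 2.2

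**Step 3: dependence on prevalence p, holding Se and Sp fixed.**

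PPV = Se·p / [Se·p + (1 − Sp)(1 − p)]

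NPV = Sp·(1 − p) / [Sp·(1 − p) + (1 − Se)·p]

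False positives per true positive = (1 − Sp)(1 − p) / (Se·p)

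At p = 5%, for example, PPV = 0.0415/(0.0415 + 0.2565) = 13.9% and the ratio is 0.2565/0.0415 = 6.2.

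The documents give no prevalence for triage use, so every row after the first is an assumption.

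| Prevalence | PPV | NPV | False positives per true positive |
|---|---|---|---|
| 13.0% (planned, at most) | 31.6% | 96.6% | 2.2 |
| 10% (assumed) | 25.5% | 97.5% | 2.9 |
| 5% (assumed) | 13.9% | 98.8% | 6.2 |
| 2% (assumed) | 5.9% | 99.5% | 15.9 |
| 1% (assumed) | 3.0% | 99.8% | 32 |

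A move from 13% to 10% already puts PPV below the lower end of the interval in step 2. The confidence interval around a table-based PPV therefore gives no idea of the uncertainty from case mix.

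**Step 4: what fixed Se and Sp leave out.** If clinicians select on suspicion, the controls they enter may differ from unselected ones, and specificity may differ too. With an assumed specificity of 90% at 1% prevalence, the ratio is 0.10 × 0.99/(0.83 × 0.01) = 11.9, against 32 at 73%. The table isolates the effect of prevalence; it does not predict performance in use.

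**The case against.** The strongest reply is that nothing in the Statistical analysis section is wrong in itself. Reporting four measures from a contingency table is standard, the article does not claim that its PPV holds elsewhere, and non-random selection is disclosed. All the measures are reported under either version of the primary outcome, so the mismatch changes no planned calculation. This stands, and it limits the severity. It does not remove the contradiction, or the gap in the reassurance about patients who are not entered.

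Three stronger readings are tempting, and the documents do not support them.

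- A reader might infer that the sample PPV will not apply to triage use, or that it will overstate PPV there. The article gives no triage-use prevalence. The Inclusion criteria describe a broad group defined by symptoms, but that is study eligibility. Secondary outcomes speaks of patients in whom rAAA is suspected, who may resemble those clinicians choose to enter. Neither the size nor the direction of any error can be fixed.
- A reader might infer that the workload model is built on the sample's false-positive fraction. Secondary outcomes names no such input, and a condensed article may leave that to the full protocol.
- A reader might take 13% as fixed by design. It is an estimate modelled from HES data, at the minimum sample size; the table will carry whatever prevalence occurs.

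It is also fair to object that Bayes re-weighting carries over sensitivity and specificity from a selected sample. That is a limit on the remedy and should be stated with it.

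**Conclusion.** The point holds in a limited form and should be fixed, though it does not threaten the study. The article contradicts itself on whether PPV is primary. Its only argument that unentered patients do not matter leaves PPV out. The raw PPV and false-positive ratio cannot be assumed to transfer, and the study cannot check whether they do, because eligible patients not entered are not captured.

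For scale, a PPV of 31.6% at the planned mix becomes 13.9% at 5% prevalence and 3.0% at 1%, while false positives per true positive rise from 2.2 to 6.2 and 32. These figures rest on the planned 83% and 73% staying constant and on prevalences that are assumed. They show how sensitive PPV is to case mix and do not estimate an actual error.

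**What to change.** 1. Align the abstract and the Primary outcome section: sensitivity and specificity primary, PPV and NPV secondary.
2. Name the population to which the predictive values are meant to apply: all eligible patients conveyed with the listed symptoms, or those in whom rAAA is suspected.
3. Label PPV and NPV from the 2x2 table as applying within the recruited sample.
4. Also report PPV, NPV and false positives per true positive by Bayes' formula from the estimated sensitivity and specificity, over a stated prevalence range, and use that range in the workload model under Secondary outcomes.
5. State that this adjusts for prevalence only, not for any effect of selection on sensitivity or specificity.

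Aggregate ambulance and HES counts would anchor the range if they can be obtained. They need a denominator of eligible conveyances outside the MI, stroke and trauma pathways and a numerator of rAAA among those same patients; HES rAAA counts alone do not supply this. Failing that, an assumed range stated openly is enough.

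The cost is a wording change, a little extra analysis and possibly a less favourable reported PPV. No patient-level data on unentered patients and no change of design are needed.

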### Smartphone triage tool

St George's Vascular Institute and the London Ambulance Service have developed a scoring system to diagnose rAAA based on ten key parameters. The score was developed with logistic regression of ambulance records and Hospital Episode Statistics (HES) data for 2200 patients from 2005 to 2010. The score used routine ambulance clinician assessments and detected rAAA with 82.6% sensitivity (area under the receiver operating characteristic (ROC) curve 0.86). The parameters collected by the app are: age, gender, blood pressure, capillary refill time, temperature, and history of collapse, back pain, diabetes, cancer or peripheral vascular disease. This triage tool has been integrated into a secure mobile app available for smartphones on all major operating systems. This mobile app has been made available to all LAS clinicians for the observational study since November 2014. LAS clinicians, including paramedics, paramedic students and technicians, will download the app onto their own personal smartphone. A website was set up to coordinate educational meetings and provide regular study updates.^18^ LAS clinicians are advised to enter physiological parameter data as soon as it is safe to do so from a clinical perspective using the first available set of observations, and in the same circumstances as completing existing patient report forms (PRFs). Pilot results show that data entry takes an average (mean) of 16 s per patient. There will be no change to the underlying logistic regression model during the course of the study, and no intention to update or modify the app thereby preventing issues with version control. The app design prevents the saving of incomplete data entry at the point of care. Incomplete patient records will be included in the analysis, where possible as per the Strengthening the Reporting of Observational Studies in Epidemiology (STROBE) guidelines. There is the possibility for incomplete data in terms of diagnosis retrieval, outcome (mortality) retrieval and discordance between the PRF data and the app data. Owing to the study design, we will not be able to follow-up eligible patients whose data are not originally included in the app. This should not prove a limitation of the study as the aim of the study is to assess the sensitivity and specificity of the model for prediction of rAAA. Assessment of any incomplete data entries will provide an outcome measure regarding potential app user error rate. This will include a sensitivity analysis whereby the ROC curve for mortality and rAAA diagnosis using each combination of ‘app data’, ‘PRF data’ and ‘app/PRF concordant data’ will be produced.

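### The removal criterion for the refined score is printed in the wrong direction (p<0.1 instead of p>0.1)

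*Protocol article*

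**What the plan says.** The rule stands in the Statistical analysis section of the protocol article. The refinement is introduced as exploratory: "The development and validation data sets will be further explored for model refinement using a logistic regression approach". The method follows, "with the same entry variables entered into forward selection", and then the thresholds: "removal from models at p<0.1, and significance ascribed at p<0.05". No p-value for entry is given; 0.05 is described only as the level for significance.

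One reported result depends on this rule: "An ROC curve will be reported for rAAA diagnosis using the original logistic score, and the refined score at the study end".

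Two other statements limit its reach. The Primary outcome section reads "To assess and validate the sensitivity and specificity of the rAAA smartphone triage tool". The Smartphone triage tool section says of the deployed score: "There will be no change to the underlying logistic regression model during the course of the study".

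**The concern.** In stepwise procedures a variable leaves the model when its p-value rises above the removal threshold, because the data then give too little support for keeping it. The printed inequality points the other way. It also conflicts with the significance level in the same phrase, since a variable cannot be significant at 0.05 and escape removal at p<0.1.

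What is at stake is the refined score. The selection rule decides which predictors it contains, and its ROC curve is to be reported beside that of the original score. A rule that cannot be followed as written does not define that score, and the analyst would have to repair the text before using it.

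**Working it through.** The disputed item is the direction of an inequality, so there is no figure in the plan to reproduce. The check is logical.

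**Inputs**, all from the Statistical analysis section: removal at p<0.1; significance at p<0.05; forward selection; entry p-value not stated.

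**Step 1: the two criteria together.** Let p be a variable's p-value in the fit to which the rule is applied.

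- Significant: p < 0.05.
- Removed, as printed: p < 0.1.
- Retained, as printed: p ≥ 0.1.

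Because 0.05 < 0.1, every significant variable falls in the removed set. The retained set (p ≥ 0.1) and the significant set (p < 0.05) have no member in common.

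**Step 2: example p-values** (chosen for illustration).

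| p | Significant at 0.05 | Printed rule (remove if p<0.1) | Corrected rule (remove if p>0.1) |
|---|---|---|---|
| 0.001 | yes | removed | kept |
| 0.03 | yes | removed | kept |
| 0.07 | no | removed | kept |
| 0.1 | no | kept | kept (boundary) |
| 0.2 | no | kept | removed |
| 0.6 | no | kept | removed |

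Only the boundary value depends on whether the correction is written p>0.1 or p≥0.1.

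**Step 3: the same rule inside forward selection.** Call the unstated entry threshold E; a variable enters when p < E.

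- If E ≤ 0.1 (for example E = 0.05, an assumption), every variable that enters has p < E ≤ 0.1 and meets the printed removal rule at once. Nothing can stay.
- If E > 0.1, only a variable with 0.1 ≤ p < E at entry escapes immediate removal, and it is not significant at 0.05.

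So whatever E is, no variable that is significant in the fit to which the rule is applied can be retained. This needs no assumption about effect sizes.

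**Step 4: what the rule reaches.**

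| Item | Uses the removal rule? |
|---|---|
| Sensitivity and specificity of the existing score (contingency table) | no |
| ROC curve of the original score | no |
| Sample size and expected confidence intervals (Power calculation) | no |
| Refined score and its ROC curve at study end | yes |

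The Power calculation rests on "over a 12-month period 150 rAAA and over 1000 controls" and on the predicted performance of the existing score, so nothing in it changes.

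**The case against.** The strongest reply is that this is a slip of sign with one plausible meaning. A removal threshold of 0.1 beside a significance level of 0.05 is a familiar pairing, and no analyst would deliberately discard predictors because they are significant. That is fair, and it limits the seriousness of the point. It does not remove it: the article states its rule, the rule is wrong as stated, and nothing elsewhere overrides it.

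A reader might infer more than the article supports:

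- **That the rule would build a score from the weakest predictors.** That describes removal from a model containing all ten variables. The article specifies forward selection, where weak variables may never enter. An illustrative simulation of one-step removal from a full model (200 runs, n=1150, about 145 events, ten independent predictors, five with a log odds ratio of 0.6 per SD and five null) gave a mean apparent AUC of 0.54 under the printed rule and 0.81 with the sign reversed. Its effect sizes are assumed and it does not follow the stated procedure, so it does not measure the effect in this study.
- **That correcting the sign later leaves the removal threshold open to choice.** It does not. The figure of 0.1 is already in the text and stays there.
- **That the entry threshold is 0.05.** The article does not say so; 0.05 may be only a reporting level.
- **That the main result is at risk.** The primary outcome concerns the existing score, which is held fixed during the study.
- **That stepwise selection should give way to penalised regression on all ten variables.** That is a preference about method, and a reversed sign is no argument for it.

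**Conclusion.** The point holds in a limited form. As printed, the removal criterion excludes every variable that meets the significance level stated beside it, so no significant predictor could remain in the refined score. This follows from 0.05 < 0.1 alone.

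The intended meaning is most likely removal at p>0.1; that is an inference from convention, not something the article states. The consequence is confined to an exploratory secondary product, the refined score and its ROC curve. No numerical effect on that curve can be derived from the article. It is a small but certain error in a stated decision rule.

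**What to change.** In the Statistical analysis section, reverse the inequality so that variables are removed from the model when p>0.1, and do so before the refinement analysis is run.

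At the same time, have the sponsor confirm the entry p-value. Even with the sign corrected, the sentence can be read as forward stepwise selection with a 0.1 removal threshold, or as forward selection with 0.1 as the cutoff for inclusion, and the two can select different models. Whatever entry value is confirmed should not exceed the removal value; otherwise a variable with a p-value between them would qualify for entry and removal at the same step.

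The cost is one line of text. No change is needed to data collection, sample size or the primary analysis.

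### As written, the refined score's ROC is in-sample but is set beside an out-of-sample ROC for the original score, so the comparison modestly favours refinement

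*Protocol article*

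**What the plan says.** The Smartphone triage tool section locks the original score: "There will be no change to the underlying logistic regression model during the course of the study". That score came from earlier data: "The score was developed with logistic regression of ambulance records and Hospital Episode Statistics (HES) data for 2200 patients from 2005 to 2010".

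The Statistical analysis section then plans an update: "The development and validation data sets will be further explored for model refinement using a logistic regression approach". The method is stepwise, "with the same entry variables entered into forward selection, removal from models at p<0.1, and significance ascribed at p<0.05". The next sentence fixes the output: "An ROC curve will be reported for rAAA diagnosis using the original logistic score, and the refined score at the study end".

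The article does not say outright which patients supply the refined score's curve. It describes only two groups, the development patients and the prospective patients, and both feed the refinement.

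**The concern.** The original score is fixed before the prospective patients are seen, so its ROC in those patients is a genuine external test. The refined score has its predictors chosen and its coefficients fitted with the same patients in whom its ROC must then be drawn. An AUC obtained that way is an apparent AUC and is biased upward. The two curves are therefore not like for like, and the difference between them leans towards the refined score even if refinement adds nothing.

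What is at stake is the reading of the two curves at study end. A score that almost always looks better than the validated one is easily preferred to it, although only the original has been tested in independent patients.

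**Working it through.** **Inputs from the protocol article**
- Candidate predictors: 10 ("age, gender, blood pressure, capillary refill time, temperature, and history of collapse, back pain, diabetes, cancer or peripheral vascular disease").
- Prospective data, Power calculation section: "over a 12-month period 150 rAAA and over 1000 controls (ie, patients found not to have a rAAA) will be studied". That is 150 / 10 = 15 events per candidate predictor.
- Development data: 2200 patients. The number with rAAA is not given; 13% (about 287) is assumed.
- Expected AUC: 0.85 ± 0.01 (Power calculation section). No figure is given for the refined score.

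**Step 1. The plan's own AUC precision.** By Hanley–McNeil, with A = 0.85, n1 = 150 and n0 = 1000:

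SE² = [A(1−A) + (n1−1)(u−A²) + (n0−1)(v−A²)] / (n1·n0), where u = A/(2−A) = 0.7391, v = 2A²/(1+A) = 0.7811 and A² = 0.7225.

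SE² = [0.1275 + 149 × 0.01663 + 999 × 0.05858] / 150000 = 61.13 / 150000, so SE = 0.020. A simulated binormal model gives 0.016. The 95% half-width is 0.032 to 0.040. The stated ±0.01 is not reproduced, so it is not used as the yardstick below.

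**Step 2. Simulation.** There were 300 replicates per setting, with 10 normal predictors and a best attainable AUC of 0.85. Pattern A has 5 real and 5 null predictors; pattern B has 10 real predictors of tapering strength. The original score is developed on 2200 patients and then frozen. The refined score comes from forward selection (entry p<0.05, removal p>0.1; the entry level is an assumption, since the article ties 0.05 to significance). Both scores are evaluated in the prospective patients (study AUC) and in the population (true AUC). Optimism is the refined score's study AUC minus its true AUC.

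| Refit on (rAAA/controls) | Pattern | Original: study / true | Refined: study / true | Optimism | Study difference | True difference | Looks better | Truly better |
|---|---|---|---|---|---|---|---|---|
| Development + 150/1000 | A | 0.8487 / 0.8483 | 0.8514 / 0.8489 | 0.0025 | +0.0028 | +0.0006 | 99% | 73% |
| Development + 150/1000 | B | 0.8450 / 0.8464 | 0.8501 / 0.8478 | 0.0024 | +0.0051 | +0.0014 | 100% | 83% |
| 150/1000 only | A | 0.8504 / 0.8482 | 0.8550 / 0.8464 | 0.0087 | +0.0046 | −0.0018 | 95% | 31% |
| 150/1000 only | B | 0.8440 / 0.8463 | 0.8514 / 0.8426 | 0.0088 | +0.0074 | −0.0037 | 98% | 17% |
| 75/500 only | A | 0.8500 / 0.8483 | 0.8575 / 0.8399 | 0.0176 | +0.0074 | −0.0085 | 90% | 9% |
| 75/500 only | B | 0.8445 / 0.8464 | 0.8540 / 0.8332 | 0.0208 | +0.0094 | −0.0133 | 87% | 0% |
| 30/1120 only | A | 0.8466 / 0.8483 | 0.8554 / 0.8277 | 0.0276 | +0.0087 | −0.0206 | 79% | 1% |
| 30/1120 only | B | 0.8472 / 0.8465 | 0.8573 / 0.8141 | 0.0432 | +0.0101 | −0.0324 | 76% | 0% |

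Differences are refined minus original. Last digits may differ from subtraction because of rounding. The 75- and 30-event rows are assumed settings, included only to show the trend.

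**Step 3. Bias in the comparison** (study difference minus true difference, 150 rAAA)
- Pooled: A, 0.0028 − 0.0006 = 0.0022; B, 0.0051 − 0.0014 = 0.0037; mean about 0.003.
- Prospective-only: A, 0.0046 + 0.0018 = 0.0064; B, 0.0074 + 0.0037 = 0.0111; mean about 0.009.

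A further check simulation agreed: about 0.003 pooled and about 0.01 prospective-only, with the lower end of the truly-better share nearer 15%.

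**Step 4. Reading.** At 150 rAAA the bias exceeds the size of the true difference in all four rows. With pooling, the refined score is usually a little better, but the gain is overstated (0.003 to 0.005 seen against about 0.001 true). With a prospective-only refit, the sign of the difference is usually wrong.

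**The case against.** The strongest reply is that reuse of the same patients is inferred. The article names no evaluation set for the refined score, and details of internal validation for a secondary model are often left to an analysis plan that is not shown. An unseen document could indeed add a correction. But the article is not merely silent here: it names the data sets, the variables, the selection rule and the output, and that sequence leaves no unused patients. Nothing in it points to a correction.

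Other parts of the reply stand, and they rule out stronger readings that a reader might infer:
- **That the bias matches or exceeds the plan's ±0.01.** Under pooling, the more natural reading of the text, it is about a quarter to a third of 0.01. The ±0.01 does not itself reproduce at 150/1000. Against the sampling SE of 0.016 to 0.020, even the prospective-only bias is small. Much of that sampling error is shared when two scores are tested in the same patients, however, so the difference between the scores is the relevant scale.
- **That the bias will be several hundredths.** That needs far fewer rAAA than the 150 the article expects, and the article states no such number.
- **That the study's main result is compromised.** The primary outcome is the sensitivity and specificity of the fixed tool, which refinement does not touch.
- **That the refined score will replace the original.** The work is described as exploratory, no formal test between the curves is planned, and the Discussion says only that the study may support a later efficacy study.

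Having no data left for external validation is normal when a model is updated on everything available. It is a reason to label the result, not an error in itself.

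**Conclusion.** The point holds in a limited form. As written, an in-sample ROC for the refined score is reported beside an out-of-sample ROC for the original, and the comparison favoured refinement in every setting examined. At 150 rAAA the bias is about 0.0025 to 0.0035 AUC with pooling and about 0.01 with a prospective-only refit. That is small in absolute terms, but enough to make the refined score look better almost always, whether or not it is. It concerns a secondary analysis only.

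The sizes rest on normal predictors, two effect patterns, about 13% rAAA in the development data, the assumed entry level, and no shift in case mix between the data sets. A real shift could make refinement truly worthwhile but would not remove the optimism.

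**What to change.** Report the refined score's AUC, sensitivity and specificity, and its paired AUC difference from the original score in the prospective patients, after optimism correction. Use the bootstrap or cross-validation, and repeat the whole procedure in each resample, including the forward selection and removal steps. State whether the refit pools the two data sets or uses the prospective patients alone. Label the refined score as not externally validated wherever its curve is shown.

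The cost is a little analysis code and a sentence or two in the plan. The refined AUC will be slightly less favourable. No new patients or data are needed, and the primary analysis does not change.
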